#### Data harmonisation

Data will be harmonised using the Stata statistical package (StataCorp, College Station, Texas), version 17. Variables of interest will be recoded to be consistent across datasets prior to combination into a single final dataset. Data harmonisation utilises the best available information. This means that patient self-reports for a given variable may be corroborated by information from family reports, medications, primary care software derived medical history and medications where available. For instance, the variable diabetes combines self-reports of the condition (yes/no), family informant reports of the condition (yes/no), and medication history (diabetic medication by self-reports or in medication review). Medication lists available for the participants will be coded using the World Health Organization’s Anatomical Therapeutic Chemical (ATC) Classification and allow for sub-analyses of outcomes in relation to medication categories of interest such as anticholinergics, analgesics, anti-psychotics and so forth [33]. The full details of variables of interest in the pooled cross-sectional dataset are provided in the appendices (Appendix 1.1).

Based on the variables of interest available in each dataset (Table 2), KHAP wave 2, KGOWS-I and TSDPS will be harmonised in cross-section, with a combined cohort of 898 Aboriginal and Torres Strait Islander participants, 244 (27%) of whom will have a diagnosis of dementia or CIND/MCI. For longitudinal analyses, data from KHAP wave 1 will be harmonised with KGOWS-I and combined with diagnoses at baseline (wave 1) and follow-up (wave 2) for analysis of factors of interest in a smaller subset of 354 participants as summarised in the appendices (Appendix 1.2). There is no longitudinal data available for TSDPS at the present time.

#### Missing data and outliers

Data harmonisation utilises the best available information to minimise missing data. In circumstances where missing data is substantial (> 5% for a single variable), imputations may be considered for predictor variables and covariates.

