**Methods/design:**

Three cohort studies - the Kimberley Healthy Adults Project (KHAP, *N* = 363), Koori Growing Old Well Study (KGOWS, *N* = 336) and Torres Strait Dementia Prevalence Study (TSDPS, *N* = 274) - share a similar research methodology with demographic, medical history, psychosocial factors, cognitive tests and consensus clinical diagnoses of cognitive impairment and dementia. Associations between risk and protective factors of interest and the presence of dementia and/or cognitive impairment diagnoses will be evaluated by univariable and multivariable logistic regression in a harmonised cross-sectional cohort of 898 participants. Factors associated with incident dementia and/or cognitive impairment will be assessed in a subset of KHAP (*n* = 189) and KGOWS participants (*n* = 165) who were available in longitudinal follow-up, after exclusion of those with baseline dementia or cognitive impairment. Analyses in relation to outcome measure of death or dementia will be conducted to account for the competing risk of death. Logistic regression will be used to evaluate the association between the individual components of the 16-component Kimberley Indigenous Cognitive Assessment (KICA) tool and the presence of dementia and cognitive impairment determined by independent consensus diagnoses. Multivariable binary logistic regression will be used to adjust for the effect of confounding variables. Results will be reported as odds ratios (OR) with 95% confidence intervals (95% CI).

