## Methods/design

### Design

The KHAP study was undertaken from 2004 to 2006 and involved 363 Aboriginal participants aged 45 and older from different communities in the remote Kimberley region of WA [1]. The KGOW study recruited 336 participants aged 60 and older from five Aboriginal communities, two from metropolitan Sydney and three in regional coastal areas of NSW between 2010 and 2012 [14]. Follow-up of participants occurred after six and seven years for KGOWS-II and KHAP wave 2, respectively. The TSDP study was conducted between 2015 and 2018 and recruited 274 participants aged 45 and older from five mainland and 18 island communities across the Torres Strait and Northern Peninsula [3]. A summary of the studies and number of participants is provided in Table 1. All three cohort studies worked in partnership with local community organisations and Aboriginal and Torres Strait Islander members and researchers to support recruitment, data collection, and feedback to communities to ensure culturally safe engagement with participants. Risk factors were collected using a structured interview protocol and encompassed demographic, medical, and psychosocial factors collected from participants and family carers where available. This comprehensive assessment was independently evaluated by a panel of clinical specialists to establish clinical diagnoses by consensus. All three cohort studies used the KICA, a screening tool for older Aboriginal and Torres Strait Islander peoples, that was validated in the remote Kimberley region of WA [15], modified for urban and regional dwellers in the form of the mKICA [16] and adapted for the Torres Strait [17]. A shortened version (KICA-Screen) has been validated for face-to-face and telehealth administration [17, 18].

**Table 1 Tab1:** Descriptive summary of landmark studies

Study/Cohort	Location	Age (years)	Sample Size (*N*=)	Participants (*n*=)
Kimberley Healthy Adults Project (KHAP)				
Wave 1 (W1) 2004–2006 [1, 8]	Remote WA	≥ 45	363	289 with normal cognition; 45 with dementia; 29 with CIND*.
Wave 2 (W2) 2011–2013 [9]	Remote WA	≥ 45	398‡	. Of 363 W1 participants, 184 completed all W2 assessments, 5 had cognitive assessment only, 109 had died and 65 declined to participate or could not be located. 105 new participants were recruited at W2. W2 cohort: 226 with normal cognition; 29 with dementia; 33 with CIND; 1 missing diagnosis; had 109 died.
Koori Growing Old Well Study (KGOWS)				

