Wave 1 (W1) 2010–2012 [2, 14, 19]	Urban & Regional NSW	≥ 60	336	249 with normal cognition; 45 with dementia; 38 with MCI†; 4 with other cognitive disorder.
Wave 2 (W2) 2016–2018 [20]	Urban & Regional NSW	≥ 60	233‡	Of 336 W1 participants, 165 were followed-up, 68 had died and 103 did not participate. W2 cohort: 105 with normal cognition; 10 with dementia at baseline; 16 with incident dementia; 34 with MCI; 68 had died.
Torres Strait Dementia Prevalence Study (TSDPS)				
Wave 1 (W1) 2015–2018 [3, 12]	Torres Strait	≥ 45	274	175 with normal cognition; 39 dementia; 60 CIND.

CIND = Cognitive Impairment No Dementia; MCI = Mild Cognitive Impairment; NSW = New South Wales; WA = Western Australia

*CIND is defined as those with a decrement in cognitive functioning that met DSM-IV-TR criteria for a cognitive or amnestic disorder but without significant loss in activities of daily living (ADL) and not attributable to a psychiatric illness or intellectual disability

† MCI diagnoses in the KGOW cohort were reclassified as CIND based on DSM IV-TR diagnoses in line with the other cohorts for analyses

‡ Sample sizes include those who have died

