#### Data analyses

Data will be analysed using the Stata statistical package (StataCorp, College Station, Texas), version 17. Analyses will be performed on harmonised cross-sectional and longitudinal data. Associations between risk and protective factors of interest and the presence of dementia and/or cognitive impairment based on consensus diagnoses will be evaluated by univariable and multivariable binary logistic regression. Analyses by dementia subtype will also be conducted to ascertain risk factors of importance between groups. In the longitudinal cohort, risk factors of interest will be determined from baseline measures (W1), compared with consensus diagnoses at follow-up (wave 2) and analysed in relation to outcome measures of incident dementia and/or cognitive impairment using univariable and multivariable logistic regression. To account for the competing interest of death (*n* = 177 before wave 2 follow-up), multinominal logistic regression will be used to estimate the association between variables of interest and the following outcomes: (1) neither cognitive impairment nor dementia nor died; (2) cognitive impairment or dementia during the study; and (3) death between baseline and follow-up. Results will be reported as odds ratios (OR) with 95% confidence intervals (95% CI). Multivariable binary logistic regression will be used to adjust for the effect of confounding variables that are anticipated to be associated with dementia such as age, sex, education and study cohort. Variables that are significant in univariable analyses will be entered into a multivariable model, after which a process of clinical judgement and examination of measures including the Akaike and Bayesian information criteria will be employed to decide which variables to retain in the final multivariable model.

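### The missing-data rule omits the wave 2 diagnosis, absent for 168 of 522 people not recorded as dead, while every death is kept, so the longitudinal odds ratios are open to selection bias of unknown size

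*Protocol article*

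**What the plan says.** Under Missing data and outliers, the article sets a trigger of more than 5% missing for a single variable and a permissive remedy: "imputations may be considered for predictor variables and covariates". Outcomes are not mentioned.

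Table 1 (under Design) accounts for everyone seen at wave 1. For KHAP: "Of 363 W1 participants, 184 completed all W2 assessments, 5 had cognitive assessment only", and "109 had died and 65 declined to participate or could not be located". For KGOWS: "Of 336 W1 participants, 165 were followed-up, 68 had died and 103 did not participate".

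Data harmonisation places the longitudinal analysis in a "smaller subset of 354 participants". Data analyses then brings in the deaths ("177 before wave 2 follow-up") through a three-category multinomial model. Its categories are alive with neither condition, impaired or demented, and "death between baseline and follow-up". Age, sex, education and study cohort are named as adjustment variables for the binary logistic models. The abstract describes the longitudinal set as formed "after exclusion of those with baseline dementia or cognitive impairment".

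Strengths and weaknesses mentions the smaller size and coarser measures of the longitudinal cohort, but not loss to follow-up.

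**The concern.** Factors associated with incident impairment are one of the two primary aims. As written, that aim is analysed only in people who were re-examined, and the one missing-data rule stops at predictors and covariates.

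The Background accepts that ignoring mortality probably affected the earlier longitudinal results, and the plan responds with a death category. Loss of people not recorded as dead (168) is nearly as large as loss to death (177), but it receives no comparable treatment.

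The two losses also enter unequally: recorded deaths are kept in full, other people only if examined. A factor that affects willingness or ability to take part at wave 2 could therefore look related to death when it is not. The impairment odds ratios could also move, under narrower conditions.

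**Working it through.** **Inputs (Table 1).** KHAP wave 1: 363; examined 184 + 5 = 189; died 109; not examined 65. KGOWS wave 1: 336; examined 165; died 68; not examined 103.

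**Reproducing the plan's figures.** Examined: 189 + 165 = 354. Deaths: 109 + 68 = 177. Both match. Each cohort closes: 189 + 109 + 65 = 363 and 165 + 68 + 103 = 336.

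**Missing wave 2 diagnoses among those not recorded as dead.**

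| | Not recorded as dead | Not examined | Retained |
|---|---|---|---|
| KHAP | 363 − 109 = 254 | 65 (25.6%) | 189 (74.4%) |
| KGOWS | 336 − 68 = 268 | 103 (38.4%) | 165 (61.6%) |
| Both | 522 | 168 (32.2%) | 354 (67.8%) |

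The outcome is thus missing at about six times the 5% trigger (32.2/5 = 6.4). The multinomial data would hold 354 + 177 = 531 of 699 people (76.0%).

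**Effect on the odds ratios.** Take the unimpaired living as the reference category. Let rU(e) and rI(e) be retention among unimpaired and impaired survivors at exposure e (0 or 1); deaths are retained with probability 1. Then:

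- observed death OR = true OR × rU(0)/rU(1)
- observed impairment OR = true OR × [rI(1)/rU(1)] / [rI(0)/rU(0)]

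The second multiplier equals 1 whenever retention is a product of an exposure part and an outcome part. It therefore moves only under joint dependence.

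**Illustrations with both true ORs equal to 1.** The retention rates are assumptions; overall retention is about 68% to 69% in each.

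| Retention, unimpaired / impaired | Impairment OR | Death OR |
|---|---|---|
| Exposure only: unexposed 74.4/74.4, exposed 61.6/61.6 | 1.00 | 0.744/0.616 = 1.21 |
| Outcome only: 72/55 in both groups | 1.00 | 1.00 |
| Joint: unexposed 74/70, exposed 68/50 | (0.50/0.68)/(0.70/0.74) = 0.78 | 0.74/0.68 = 1.09 |
| Stronger joint: unexposed 74/74, exposed 70/45 | (0.45/0.70)/(0.74/0.74) = 0.64 | 0.74/0.70 = 1.06 |

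**The mechanism in the article's own counts.** The crude KHAP-versus-KGOWS odds ratio for death against all others is (109/254)/(68/268) = 1.69 in everyone seen at wave 1. It is (109/189)/(68/165) = 1.40 when only examined people stand beside the deaths. The two differ by the retention ratio, 0.744/0.616 = 1.21.

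**Limit of the denominator.** At wave 1, 289 + 249 = 538 people had normal cognition and 45 + 29 + 45 + 38 + 4 = 161 did not. Deaths and losses are not split by baseline diagnosis. The 354 is itself an unrestricted total: the KGOWS 165 breaks down as 105 + 10 + 16 + 34, where the 10 had dementia at baseline. So 32.2% is not the figure for the at-risk set, which cannot be derived from the article.

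**The case against.** **Bias is possible, not shown.** A reader might infer from 32% loss that the longitudinal odds ratios are biased. The article does not support that. The impairment odds ratio survives retention that depends on exposure alone or on outcome alone, and no retention by risk factor or by baseline cognition is reported. It is plausible that frailer people were lost, but nothing in the article documents it. This objection stands and limits the conclusion.

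**The one visible difference is between cohorts.** The shift from 1.69 to 1.40 belongs to cohort, which is an adjustment variable and not a risk factor of interest. That stands too: where cohort is in the model, this part is largely absorbed. It is not a complete answer. Cohort is named for the binary models, and the multinomial covariates are not stated. Variables are screened on univariable significance before any adjustment. Differential participation within a cohort is untouched.

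**Absolute risks.** A reader might also note that deaths are 177/531 = 33% of the analysed set against 177/699 = 25% of the cohorts, and conclude that risks are distorted. The plan reports odds ratios only, so no planned estimate is affected in that way.

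**The analysis plan may deal with it.** A registered plan and an appendix on the longitudinal data exist but are not shown, and the wording is permissive. Simple silence would be no finding. Here, however, the article states a rule with a trigger and a scope, and that scope leaves out the variable with the largest documented loss.

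**Conclusion.** The point holds as a gap in a stated rule, not as demonstrated bias. Before baseline exclusions, 168 of 522 people not recorded as dead (32%) have no wave 2 outcome, and the rule as written leads to complete-case analysis of that outcome beside all 177 recorded deaths.

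Two consequences follow. In the multinomial model, participation that varies with a factor among unimpaired survivors is enough to shift that factor's death odds ratio, by the retention ratio; a contrast as large as that between the cohorts would give 1.21 from a true 1.0. The impairment odds ratios are exposed only under joint dependence on exposure and outcome; the assumed examples gave 0.78 and 0.64 from a true 1.0. Within cohort, the actual size and direction are unknown.

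This rests on category 1 being the reference and on deaths being fully recorded. The KHAP 65 include people who could not be located, some of whom may have died.

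**What to change.** Amend Missing data and outliers and Data analyses as follows.

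1. Restrict the longitudinal set to those free of dementia and cognitive impairment at wave 1, and give examined, dead and not-examined counts for that set by cohort.
2. Weight examined survivors by the inverse of their estimated probability of wave 2 participation given survival, modelled on wave 1 data: age, sex, cohort, education, KICA or mKICA score within cohort (the versions differ), mobility and comorbidity. Recorded deaths keep a weight of 1. Use robust or bootstrap intervals. Alternatively, multiply impute wave 2 status from the same variables.
3. Report complete-case results alongside, with a table comparing retained and lost participants on wave 1 characteristics.
4. If the KHAP data separate refusal from failure to locate, add a sensitivity analysis that treats the non-located as deceased.

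The cost is modest extra analysis on data already collected and slightly wider intervals. Weighting and imputation both assume that participation is explained by the wave 1 variables used, so they reduce the risk of bias but do not remove it.

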#### Data analyses

Data will be analysed using the Stata statistical package (StataCorp, College Station, Texas), version 17. Analyses will be performed on harmonised cross-sectional and longitudinal data. Associations between risk and protective factors of interest and the presence of dementia and/or cognitive impairment based on consensus diagnoses will be evaluated by univariable and multivariable binary logistic regression. Analyses by dementia subtype will also be conducted to ascertain risk factors of importance between groups. In the longitudinal cohort, risk factors of interest will be determined from baseline measures (W1), compared with consensus diagnoses at follow-up (wave 2) and analysed in relation to outcome measures of incident dementia and/or cognitive impairment using univariable and multivariable logistic regression. To account for the competing interest of death (*n* = 177 before wave 2 follow-up), multinominal logistic regression will be used to estimate the association between variables of interest and the following outcomes: (1) neither cognitive impairment nor dementia nor died; (2) cognitive impairment or dementia during the study; and (3) death between baseline and follow-up. Results will be reported as odds ratios (OR) with 95% confidence intervals (95% CI). Multivariable binary logistic regression will be used to adjust for the effect of confounding variables that are anticipated to be associated with dementia such as age, sex, education and study cohort. Variables that are significant in univariable analyses will be entered into a multivariable model, after which a process of clinical judgement and examination of measures including the Akaike and Bayesian information criteria will be employed to decide which variables to retain in the final multivariable model.

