### Data for harmonisation

#### Dementia diagnosis

Diagnoses in each of the studies were based on data obtained through comprehensive medical assessment inclusive of medical, behavioural, neurological, cognitive and collateral caregiver measures performed by a trained specialist (geriatrician, older person psychiatrists, general physician) in dementia assessment. De-identified data from clinical assessments were reviewed by a panel of specialists to obtain consensus diagnoses based on the Diagnostic and Statistical Manual for Mental Disorders, 4th Edition (DSM IV-TR) [24]. Dementia subtypes of Alzheimer’s, vascular, mixed, or other were specified where possible. For the purpose of analyses, participants were reclassified based on DSM IV-TR diagnoses as having normal cognition, dementia, MCI [2] or CIND [8, 12]. The CIND and MCI groups demonstrated a decrement in cognitive functioning that met DSM-IV-TR criteria for a cognitive or amnestic disorder that was not attributable to a psychiatric illness or intellectual disability, but without significant loss in activities of daily living (ADL). For the harmonised dataset, MCI diagnoses in the KGOWS cohort were reclassified as CIND based on DSM IV-TR diagnoses in line with the other cohorts for analyses. Dementia subtypes of Alzheimer’s, vascular, mixed, or other were specified where possible based on the DSM IV-TR.

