#### Variables of interest

Risk and protective variables of interest associated with dementia are derived from the 2020 Lancet report, the World Health Organisation (WHO) guidelines, Cardiovascular Risk Factors Aging, and Incidence of Dementia (CAIDE) index, and Australian National University Alzheimer’s Disease Risk Index (ANU-ADRI) and summarised in Table 2. These are life-course risk and protective factors for dementia in the general population and well established in the literature [13, 25–27]. We have included these measures for analysis across the three studies to establish whether the same risk factors are relevant to Aboriginal and Torres Strait peoples. Studies have also shown that certain syndromes such as falls, executive dysfunction, depressive symptoms and urinary incontinence may be more common in older people with cerebral white matter changes suggestive of cognitive vulnerability and impairment [28, 29]. Measures of mobility impairment, falls, sleep disturbance, urinary incontinence, and impairments in ADLs will be included to look at these syndromes. Additionally, history of cardiovascular, renal, or cerebrovascular disease inclusive of stroke or a transient ischaemic attack are included as markers of vascular comorbid conditions.

**Table 2 Tab2:** Compilation of risk factors of interest based on existing literature

Measure	Data available
Less education (< 10 years) *†‡§	Simple measure in KHAP W1. Levels of education available in KHAP W2, KGOWS and TSDPS.
Hearing impairment*	Yes
Physical inactivity/exercise *†§	Simple measure available in KGOWS but not in KHAP or TSDPS
Cognitive stimulation †§	Skilled work/jobs as a proxy measure in KGOWS only
Head injury with loss of consciousness *§	Yes
Diabetes †*§	Yes
Hyperlipidaemia/ high cholesterol †‡	KHAP W2, KGOWS and TSDPS only
Hypertension *†‡	Yes
Infrequent social contact/social isolation *†§	Only available from KGOWS data Subjective loneliness, living alone, social activity participation in prior 3 months for 10 activities
Diet (e.g. fish intake) †§	No
Alcohol consumption *†§	Yes
Air pollution *	No
Smoking *†§	Yes
Obesity (Body mass index > 30) †*‡	Only in KHAP W2 and KGOWS
Depression/Depressive symptoms *†§	Yes
Older Age ‡§	Yes
Sex §	Yes

* Dementia prevention, intervention, and care: 2020 report of the *Lancet* Commission [26]

†World Health Organisation (WHO) guidelines [30]

‡ Cardiovascular Risk Factors Aging, and Incidence of Dementia (CAIDE) Risk Score [31]

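### Odds ratios of stroke and cerebrovascular history by dementia subtype would partly reflect how the panel labelled the subtypes, because the panel reviewed the same medical history

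*Protocol article*

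**What the plan says.** Four statements in the protocol article bear on this.

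- **Predictors.** Variables of interest adds vascular disease to the candidate list: "history of cardiovascular, renal, or cerebrovascular disease inclusive of stroke or a transient ischaemic attack are included as markers of vascular comorbid conditions". Design describes the source: "Risk factors were collected using a structured interview protocol and encompassed demographic, medical, and psychosocial factors".
- **Material behind the diagnosis.** Dementia diagnosis says diagnoses rested on "comprehensive medical assessment inclusive of medical, behavioural, neurological, cognitive and collateral caregiver measures" and that "De-identified data from clinical assessments were reviewed by a panel of specialists to obtain consensus diagnoses". Design, directly after describing the interview and its risk factors, says: "This comprehensive assessment was independently evaluated by a panel of clinical specialists to establish clinical diagnoses by consensus".
- **Subtype.** "Dementia subtypes of Alzheimer’s, vascular, mixed, or other were specified where possible based on the DSM IV-TR". No further rule is given.
- **Analysis.** Data analyses plans the comparison: "Analyses by dementia subtype will also be conducted to ascertain risk factors of importance between groups". It removes no variable of interest from it.

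No section says that the panel was masked to stroke or other vascular history. Strengths and weaknesses discusses causality, the size of the longitudinal cohort and unavailable risk factors, but not this overlap.

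**The concern.** A vascular or mixed label is, on its face, a judgement that cerebrovascular disease contributed to the dementia. A panel with the medical history in front of it would be expected to give that label more often when there had been a stroke. If stroke history is then used as a predictor of the label, the exposure has helped to form the outcome. This is incorporation bias. It works in both directions: stroke-positive cases are drawn into the vascular or mixed group and out of the others, so stroke can look neutral or protective for Alzheimer's disease. Adjustment for age, sex, education and cohort, as planned, does not remove it.

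The consequence is in interpretation. The abstract names vascular risk beyond stroke as a gap, and Background points to limited data on risk factors for vascular dementia, so readers will look to the subtype results for an answer. The Discussion also envisages a brain-health assessment tool built on the factors identified. An odds ratio below 1 for stroke in Alzheimer's disease could be reported as a finding when it comes from the sorting of cases.

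**Working it through.** **1. The plan's own figures.** The cross-sectional dataset combines KHAP wave 2, KGOWS wave 1 and TSDPS (Data harmonisation). From Table 1:

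- Total: (226 + 29 + 33) + (249 + 45 + 38 + 4) + (175 + 39 + 60) = 288 + 336 + 274 = 898, leaving out the one missing KHAP wave 2 diagnosis. This matches the stated 898.
- Dementia or CIND/MCI: (29 + 33) + (45 + 38) + (39 + 60) = 244, and 244/898 = 27.2%. This matches the stated 244 (27%).
- Dementia: D = 29 + 45 + 39 = 113. Normal cognition: N = 226 + 249 + 175 = 650.

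The article gives no subtype counts, stroke prevalence or labelling rule. The rest is an illustration under assumptions.

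**2. Set-up.** Let stroke history have the same prevalence s among dementia cases and people with normal cognition, so the true odds ratio is 1. Let the panel label a case vascular or mixed with probability a if there is a stroke history and b if there is not. Take normal cognition as the reference group.

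**3. Formulas.**

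- Vascular/mixed v normal: [D·s·a × N(1−s)] / [D(1−s)·b × N·s] = a/b
- Other subtypes v normal: (1−a)/(1−b)
- Vascular/mixed v other subtypes: a(1−b) / [b(1−a)]

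D, N and s cancel, so the results do not depend on the counts or on stroke prevalence.

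**4. Results.**

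| a (stroke) | b (no stroke) | Vascular/mixed v normal | Other subtypes v normal | Vascular/mixed v other |
|---|---|---|---|---|
| 0.3 | 0.3 | 1.0 | 1.0 | 1.0 |
| 0.5 | 0.2 | 2.5 | 0.625 | 4 |
| 0.7 | 0.1 | 7.0 | 0.33 | 21 |
| 0.9 | 0.05 | 18 | 0.11 | 171 |

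The first row is a panel whose labelling ignores stroke history, and there is then no bias. Every other row shows an association created by labelling alone.

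**5. If stroke is a real risk factor.** With an all-cause odds ratio R that is the same before labelling, the first two formulas become R·a/b and R(1−a)/(1−b). Assume stroke in 25% of dementia cases and 10% of people with normal cognition: R = (0.25/0.75)/(0.10/0.90) = 3.0. Then:

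- a = 0.8, b = 0.1: 3 × 0.8/0.1 = 24 for vascular/mixed; 3 × 0.2/0.9 = 0.67 for the rest.
- a = 0.9, b = 0.1: 3 × 0.9/0.1 = 27; 3 × 0.1/0.9 = 0.33.

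A threefold all-cause association thus becomes a very large one in one group and an inverse one in the other. These two cases assume strong labelling.

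**6. Incomplete subtyping.** Subtypes were assigned only where possible. If a and b are read as probabilities among subtyped cases, and being subtyped does not depend on stroke history, the formulas are unchanged.

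**The case against.** The strongest reply is that Data analyses gives subtypes a single sentence. It names no predictor, reference group or contrast, so the entry of stroke into those models is inferred. The article refers to a registered statistical analysis plan and to Appendix 1.1 for variable details, and either might deal with this. The inference is acknowledged. But the article itself commits to comparing risk factors between subtypes and lists stroke/TIA and cerebrovascular history among them without restriction. The problem is a stated comparison that gives an uninterpretable estimate, which is more than an unwritten detail.

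A second reply is that the panel worked independently. Independent evaluation does not mean masking to the history, and the text says that the panel evaluated the assessment itself.

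Other parts of the case against do stand:

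- **Labelling rule.** The article does not say how much weight stroke history carried. That the panel could use it is supported; that stroke defines the subtype is not shown.
- **Reach.** Subtype analysis is not named among the primary or secondary outcomes in Study aims.
- **Remedy.** Reporting the stroke odds ratios with an explicit limitation would be a weaker alternative to leaving them out.

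A reader might also infer that all the subtype odds ratios are circular. The documents do not support that: subtype results for a factor such as sex do not share this problem. Nor do they show that a stroke association with vascular dementia would be wholly an artefact, since stroke may contribute to it. It might further be inferred that the hypertension and diabetes estimates are distorted. That is possible if the panel weighed those histories, but neither size nor direction can be shown from the article.

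**Conclusion.** The point holds in a limited form. Followed as written, the plan yields odds ratios of stroke and cerebrovascular history, by subtype and between subtypes, that mix aetiology with the panel's labelling. The same may apply to other vascular history that the panel weighed. All-cause dementia and dementia/CIND analyses are not affected in this way.

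The direction needs only that the panel labelled stroke-positive cases vascular or mixed more often than stroke-negative ones. The size is unknown. With no true association, the assumed labelling probabilities give odds ratios of 1.0 to 18 for vascular or mixed dementia and 1.0 down to 0.11 for the other subtypes. A reader might take the values of 24 to 27 and 0.67 to 0.33 as the expected result. They are not: they need an assumed all-cause odds ratio of 3.0 and strong labelling, and they lie at one end of the possible range.

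The change is worth making: it is small, and neither the planned adjustment nor the stated limitations deal with the overlap.

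**What to change.** - **Data analyses:** state that stroke/TIA and cerebrovascular disease are not entered as predictors in the subtype models, that they are tested only against all-cause dementia and dementia/CIND, and that their frequency by subtype is reported as a description of how cases were diagnosed.
- **Same section:** label subtype results for other vascular-history factors, such as hypertension, diabetes, cholesterol and kidney disease, as exploratory, and note that the panel had the medical history.
- **Strengths and weaknesses:** add that the subtype diagnoses and the vascular history come from the same assessment.

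The cost is a few sentences and no new data. What is lost is the stroke-by-subtype odds ratios, which could not be read as aetiological; the all-cause stroke estimates are kept.
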